## 10. Privacy Protections

All face-to-face screening interviews and face-to-face in-depth interviews will take place in a private room either at the probation, parole or an ATI program site, a Fortune site or at our community research site.

All ACASI (Audio Computer-Assisted Self Interview) interviews will take place in an enclosed cubby space or kiosk with head phones so that others may not hear questions or view responses. Although some research activities may take place within a criminal justice setting, all information collected in the interview is confidential, and will not be shared with any criminal justice entity. This includes information about illegal activity, such as drug use. Probation, parole or ATI program department personnel have affirmed that they will not seek identifiable information on research participants. The only instance where research staff are required to release identifiable information is in the case of imminent harm to yourself or others, or if there is a report of child abuse or neglect. We have obtained an assurance letter from Fortune Society and Memorandum of Understandings (MOUs) from the NYC Departments of Probation, Parole and designated ATI programs providing assurance that they will not seek the data collected about subjects. The general letter of introduction will be composed for the intervention team to introduce them to the supervisors of each probation, parole or an ATI program site where recruitment is to occur, with instructions to provide a copy of the letter to all probation, parole or ATI program officers at each such site. The researchers have taken steps to assure privacy and the confidentiality of the information provided by the participants. These steps include obtaining a Certificate of Confidentiality and the assurance of Fortune Society that it will not disclose any information to others or seek access to it. Further, probation, parole or ATI program sites will not have any documents linking the participants name to any information given to the researchers. In the criminal justice system, however, there are no absolute guarantees of confidentiality. If participants have signed a waiver of confidentiality or release (or sign one in the future), the holder of such a waiver or release may seek to obtain information from the researchers. The researchers will resist disclosure of such information by all lawful means.

All study staff will undergo a common training that includes the impetus, goals, organization, and rules/regulations under which the study operates; this common "base" training also covers:

(1) ethical issues in research; (2) establishing and maintaining rapport with participants; (3) obtaining informed consent; (4) addressing participants' concerns with confidentiality and handling sensitive situations; (5) obtaining accurate tracking information; (6) managing distress and conducting crisis and enhanced referrals; and (7) detecting, handling, and reporting adverse events. This common, general training is supplemented with more specialized topics and scenarios during trainings dedicated to specific roles/tasks (e.g., Fortune providers or RAs who deliver HIV/STI results) as appropriate.

**Confidentiality of in-depth interviews with Probation, Parole or ATI program staff and Fortune providers:** In addition, for the purposes of improving this program, participants will be audio taped in the sessions and/or audio taped during an interview session. Only research staff will review these tapes. The tapes are for research and training purposes only, and will be erased after the study is completed. Interviewing records will only be shared with the research team. Recordings will be downloaded to a secure and password protected for storage and then erased from the digital recorder. The recording will be reviewed by a research assistant for accuracy and thematic analysis. Any identifying from the defined by the Health Insurance and Portability Act (HIPAA) will be immediately deleted from the recording. All digital recordings will be destroyed at the end of the study after they have been transcribed and the transcriptions have been checked for accuracy. All electronic files transcripts and thematic analyses of transcripts will be encrypted and password protected.

**Disclosure Protocol:** By virtue of the study population, it is anticipated that some of the subjects may disclose past or current engagement in law breaking activity (e.g., sex trading, selling drugs, theft, etc). Following protocols used in the pilot study and prior SIG research with drug-involved offenders, research staff and Fortune providers will inform participants of the limits of confidentiality at the start of session. Research staff will not release any information about participant to anyone unless there is a possibility of "imminent harm to self or others" and/or, through group or individual discussions it becomes clear that a child is in danger or is experiencing physical abuse or neglect. [name] has secured a Certificate of Confidentiality from DHHS to avoid subpoena regarding confidential information from subjects upon receipt of funding for this study.

**Suicidal and Homicidal Respondents:** Confidentiality cannot be maintained if a participant is homicidal or demonstrates intent on seriously injuring another person. Similarly, a respondent may indicate that he is considering hurting himself. Following protocols used in prior SIG studies intervention trials with populations at elevated risk for HIV/STI transmission, we will inform the appropriate agency (e.g., law enforcement, hospital) in these cases. Research assistants will be trained to handle either situation in the event it occurs, and these procedures will be described in the informed consent forms and reviewed with all participants during consent procedures. Like the procedures for referrals, data regarding implementation of procedures to address suicidal/homicidal participants will be collected and analyzed in a parallel manner to investigate the effects of the research process itself on utilization/involvement with the service system and other outcomes.

**Child Abuse/Neglect:** By law, the privilege of confidentiality does not extend to information about the sexual or physical abuse or neglect of a child. If a participant makes statements from his personal knowledge, which if correct, would render a child abused or neglected, New York City's Administration for Children's Services (ACS) will be notified. The PI will make every

effort to attempt to ensure the safety of participants. Participants will be informed of these mandates during administration of the informed consent protocol. Like the procedures for referrals and suicidal/homicidal participants, data regarding implementation of procedures to address child abuse/neglect will be collected and analyzed in a parallel manner to investigate the effects of the research process itself on utilization/involvement with the service system and other outcomes.

## 11. Potential Risks

Screening, assessments, and interventions should pose minimal risks to subjects participating in the study. Subjects may become embarrassed or uncomfortable while being asked questions and there is some risk that discussing sensitive topics will cause distress. Because subjects will take part in a group intervention, there is a risk that other group members may divulge confidential information to people outside the group. We will address this by asking everyone to respect the confidentiality of the other participants. Participants will be advised that conversations about HIV and safer sex negotiation may anger their male partners. This anger may put them at risk for emotional, physical and/or sexual abuse or abandonment of the relationship. Participants will be advised to observe any signs of such anger in their partners and to discuss them with study staff immediately.

Study staff will be trained to provide crisis intervention and referral for such situations as follows: All project staff will be trained to observe verbal and non-verbal signs that may indicate that the respondent is emotionally distressed. In cases where the respondent is exhibiting distress, the data collector, recruiter, or facilitator will acknowledge that the questionnaire or group session can raise troubling issues for respondents and ask the respondent how she is feeling and whether or not she wants to take a break from the interview/group. If the respondent continues to exhibit distress, the data collector/recruiter/facilitators will ask her if she wants to terminate the interview or session and encourage her to discuss the issues further with any existing counselor. If a respondent seems unresponsive or unwilling to go to the counselor, or if there is no current counselor, the researcher staff will offer her a range of counseling options in the local community, using a resource manual developed for this project that contains local services and resources with up-to-date contacts who have indicated a willingness to serve women from our study population. Project staff will refer participants who request such services to professionals who we have identified in the community. After assisting the participant in exploring the counseling, residential and/or legal services available, the facilitator will offer to assist the participant in locating appropriate services and will provide enhanced referrals (e.g., calling the organization and assisting in making an appointment). If the participant is undecided about needing help and is not ready to take a referral, the facilitator will give the participant a business card with the phone number of the Project Director and encourage her to call if she would like a referral in the future. Acute emergency distress referrals will be directed to the designated counselor or social worker, and the Project Director and [name], who is a certified social worker, will be alerted. In the event that a respondent indicates to research staff that she is suicidal or homicidal, a designated clinic counselor or a SIG certified mental health professional will be informed and available for crisis intervention. At the end of all assessment and intervention sessions, whether or not complete, staff will ask anxious or troubled participants for permission to discuss their discomfort with their treatment program counselors. If permission is granted, research staff will walk distressed participants directly to the counselor. Any participant choosing not to be referred to their counselor will receive counseling from trained

certified professional mental health counselors on the research team, including the PI, Co-Investigators, and the Project Director, available as back-up to treat and make enhanced referrals for distressed participants.

Additionally, risks from this project may arise from obtaining specimens, or from conducting a rapid oral HIV test. Women may feel uncomfortable providing specimens for STI testing, providing an oral swab to test for HIV, or receiving pre- and post-test counseling for HIV. This project also involves risks that are associated with positive STI and HIV testing. The possible diagnosis of an STI or HIV and partner notification could cause emotional distress. Although unlikely, breach of confidentiality regarding STI status, HIV serostatus, sexual behaviors and relationships resulting from participation in this intervention may cause participants some level of psychological, social or financial distress. There is a possibility of unauthorized disclosure of sensitive information shared during screening, intervention sessions, or assessments. To minimize the likelihood of unintended disclosure and to maintain confidentiality safeguards, research staff will be trained to remind participants that they may at any point request their data be destroyed without question. Additionally, the NYC Departments of Probation, Parole and designated ATI program sites have indicated in letter of supports that they will not request any participant information obtained through the study. By virtue of the study population, it is anticipated that some of the subjects may disclose past or current illegal activity (e.g. sex trading, drug activity, theft, etc.). Other possible types of information disclosed are intimate partner violence, suicidal or homicidal ideation, or child abuse/neglect. Following protocols used in prior SIG research with drug-involved offenders, research staff will not release any information about participants to anyone unless there is a possibility of imminent harm to self or others and/or actual or suspected child abuse or neglect.

### 11.1 Vulnerable Populations

The proposed study will not involve participants who meet the criteria for classification as prisoners. As the study will involve participants who are in probation, parole or ATI programs, there is a likelihood that some participants may become incarcerated. If a participant becomes incarcerated or detained, the adverse events protocol described below will be followed, and the participant's involvement in the study will be discontinued.

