### 1.2. Primary Aims

1. To test the comparative effectiveness of E-WORTH versus Streamlined HIV Testing on primary outcomes of decreasing biologically confirmed STIs and the number and proportion of unprotected sexual acts at the 12-month follow-up and secondary outcomes of reducing drug use, increasing utilization of drug treatment, linkage to HIV care and ART adherence (for HIV+ participants), decreasing partner violence and recidivism.
2. To test if the effectiveness of E-WORTH on study outcomes is moderated by client characteristics (e.g. client subgroups defined by socio-demographics and psychosocial characteristics)
3. To estimate the costs and comparative cost-effectiveness of E-WORTH versus Streamlined HIV Testing on STI infection rates, drug use and projected number of HIV cases averted at the 12-month follow-up.

4. To examine qualitatively and quantitatively how multi-level theory-driven factors may influence the fidelity of implementation and effectiveness of E-WORTH and Streamlined HIV testing on study outcomes.

1.3 Rationale: Despite extremely high rates of HIV and STIs that have been found among women on probation, parole or ATI programs nationwide, to date, WORTH is the only intervention that has been found to be efficacious in increasing condom use and reducing sexual risks among justice involved women in the U.S. Our recent study of 337 drug-involved women on probation or community supervision in NYC found that 17% of the 221 Black women tested positive for HIV and 30% tested positive for an STI . The HIV rate found among Black women on probation indicates a highly concentrated epidemic, comparable to rates in sub-Saharan Africa; however, no HIV prevention or testing services are provided in NYC probation sites. The proposed study will address this critical gap in services for Black women drug users in probation settings by testing the effectiveness and cost-effectiveness of the 5-session multimedia E-WORTH intervention.

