**2.3 Power Analyses:** From ICC estimates based on the previous WORTH trial, variance inflation factors were calculated to generate effective sample sizes used in G\*Power for Aim 1. For cumulative STI incidence, we assumed a 50% reduction (on a background cumulative incidence of 20.5%) to be clinically meaningful to detect via Poisson regression; for behavioral outcomes, projected means, standard deviations, allow for effect size  $f^2$  to be calculated and used in G\*Power. Results for primary outcomes (Figure 3) indicate that 80% power is achieved for the rate-limiting outcome (i.e., cumulative STI incidence) with an effective sample size of 372 participants; translating to a sample size of 378 participants after accounting for ICC. We then increased the starting sample size to 420 to safeguard against attrition (modeled as a complete loss of 10% of data as conservative estimate since the efficacy trial of WORTH achieved a 91% retention rate at 12-month follow-up and many of those cases provided data at earlier assessment points, thus were not “fully” missing). For secondary outcomes, power analyses participants/arm indicate 80% power to detect differences for effect sizes  $f^2 = .03$  to  $.04$  (for  $\alpha = .1$  TO  $.5$ ) with sample sizes as low as 369.

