#### 3.4. Assessments:

Participant Assessment for Aim 1: When a participant arrives for their pre-intervention assessment, they will undergo a shortened version, 5 minutes, of the screener to confirm eligibility. If a woman no longer meets eligibility criteria, she will be compensated \$10 and will no longer participate in the study. Women who meet eligibility criteria will undergo a pre-intervention assessment. This assessment will last approximately 60 minutes, consisting of demographic information, history of criminal justice involvement, drug and alcohol use and dependence, sexual and drug-related HIV behaviors, HIV treatment and care, intimate partner violence, depression and PTSD, service utilization, and social support. RAs will schedule repeated assessments with participants that will take place at baseline and at 3, 6, and 12 months post- intervention. For all assessments, participants will complete the ACASI surveys on computers with headphones at a computer work station designed for privacy so that others cannot see their responses on the computer. Participants will be given the option to complete the baseline survey at SIG's community research office at [name] or on site at Probation, parole or designated ATI program or Fortune Society sites.

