#### 5. Study Questionnaires

The following questionnaires are attached to the IRB protocol:

**Screening Questionnaire:** The eligibility questionnaire will be administered in a face-to-face interview by a trained RA. The screening interview will take approximately 15 minutes. Before completing the baseline, an RA will administer a face-to-face interview with selected eligibility items from the Questionnaire to confirm eligibility of participants.

**Baseline/Follow up assessment:** This assessment will be used for baseline as well as 3-, 6- and 12-month follow up assessments.

- **Immediate post-intervention evaluation questionnaire:** This evaluation questionnaire will be administered individually at the end of the final session for E-WORTH participants and at the end of the streamlined HIV testing alone session for participants assigned to this condition. There is an evaluation form specific for both intervention arms.

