Serious adverse events include death, a life-threatening event, an event resulting in hospitalization, prolongation of hospitalization, disability, and incarceration. Serious adverse events, regardless of whether or not they are study related, will be reported to the Columbia University IRB. Other adverse events include breaches of confidentiality (both intentional - e.g., mandated reporting of suicidal/homicidal participants - and unintentional), and non-life threatening psychological distress. The PIs will closely monitor adverse events. The investigative team is aware that the study sample is likely to experience a relatively high incidence of adverse events due to their past/current history of law-breaking behavior, rates of recidivism/re-incarceration reported in the literature, and the high levels of service needs noted earlier in this application. Drawing upon past and ongoing SIG studies, the investigative team designed two forms, (1) Adverse Event: Initial Report and (2) Adverse Event: Full Report, to document adverse events, staff responses, and disposition. The procedures used to track, report, and examine adverse events are described below.

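### Women who are jailed or detained leave follow-up although recidivism is a secondary outcome, so custody known to staff goes missing from that outcome because it happened

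*Supplement*

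**What the plan says.** Section 1.2 lists "decreasing partner violence and recidivism" among the secondary outcomes of Aim 1. Section 3.4 describes a self-interview that covers "history of criminal justice involvement", and Section 5 says of the instrument: "This assessment will be used for baseline as well as 3-, 6- and 12-month follow up assessments". No definition of recidivism is given, and no arrest, court or jail record is named as a source for it.

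Section 11.1 first states that the study will not involve people classified as prisoners and then accepts that "there is a likelihood that some participants may become incarcerated". The rule follows: "If a participant becomes incarcerated or detained, the adverse events protocol described below will be followed", and the woman's "involvement in the study will be discontinued".

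Section 12 expects adverse events to be relatively frequent, partly because of re-incarceration, and defines seriousness this way: "Serious adverse events include death, a life-threatening event, an event resulting in hospitalization, prolongation of hospitalization, disability, and incarceration". The report form takes the date, description and duration. A participant discontinued because of an adverse event is monitored for the status of that event only, until it resolves or is judged unrelated to the study.

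On analysis, Section 2.2 and the Data Analyses Plan specify intention to treat, multiple imputation, complete-case analysis, attrition analyses and sensitivity analyses. None of these mentions incarceration.

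**The concern.** Removal from follow-up is triggered by an event that is itself a form of one of the outcomes. Whether the recidivism item is observed then depends on its own value. Standard imputation, which assumes that missingness depends only on observed data, does not repair this unless the incarceration record is in the model.

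The primary outcomes are exposed too. The Data Analyses Plan tests new STI at 12 months, and in Section 3.7 the 12-month visit is the only follow-up visit whose payment line includes an STI test. A woman detained briefly in month 2 and discontinued would have no 12-month swab and no later data on condomless sex. If E-WORTH changes the chance of detention, this loss differs between arms.

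**Working it through.** **1. The sections side by side**

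| Question | Where | Answer |
|---|---|---|
| Is recidivism an outcome? | 1.2 | Yes, secondary |
| How is criminal-justice involvement measured? | 3.4, 5 | Self-interview at baseline, 3, 6 and 12 months |
| What happens on detention? | 11.1 | Adverse event protocol, then involvement ends |
| Is a return after release provided for? | 11.1, 12 | None stated |
| Is incarceration recorded elsewhere? | 12 | Yes, as a serious adverse event |
| Does that record feed the recidivism outcome or the imputation? | 2.2, 12, Data Analyses Plan | Not stated |

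The event is known to the study. It is absent from the described outcome measure, not from all trial records.

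**2. Direction of the bias (assumed rates, because the documents give none)**

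Take 210 women per arm, custody risk 20% in control and 10% in E-WORTH, and a further 10% in each arm re-arrested without custody. Assume that every detention is known before the next assessment.

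- True recidivism: (42 + 21)/210 = 30% v (21 + 21)/210 = 20%, a difference of 10 points.
- Retained women: 210 − 42 = 168 v 210 − 21 = 189.
- Observed in retained women: 21/168 = 12.5% v 21/189 = 11.1%, a difference of 1.4 points.
- If recidivism meant custody alone, the observed figures would be 0% v 0% against a true 20% v 10%.

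Halving the custody risks (10% v 5%) gives an observed difference of 0.6 points against a true 5. Raising them to 30% v 15% gives 2.5 against 15.

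**3. The plan's sample size (Section 2.3), reproduced first**

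- Inputs: control incidence 0.205; 50% reduction, so 0.1025; effective N 372; N after clustering 378; loss 10%.
- Attrition: 378/(1 − 0.10) = 420, exact. The allowance is 0.10 × 420 = 42 women.
- Inflation for clustering: 378/372 = 1.016.
- Poisson-regression formula, two-sided 0.05, 80% power: N = (1.96√4 + 0.8416√6)²/(0.205 × (ln 0.5)²) = 35.78/0.0985 = 364 rounded up, within 3% of 372.

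The plan's figures are not in dispute.

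**4. Power for the STI outcome at larger total loss**

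Two-proportion approximation, with n per arm = 210 × (1 − loss) × 372/378:

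power = Φ{[0.1025 − 1.96√(2 × 0.15375 × 0.84625/n)] / √[(0.205 × 0.795 + 0.1025 × 0.8975)/n]}

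| Total loss | n per arm (effective) | Power |
|---|---|---|
| 10% | 186.0 | 78.5% |
| 15% | 175.7 | 76.1% |
| 20% | 165.3 | 73.6% |

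The 78.5% at the planned loss, against the stated 80%, reflects this approximation rather than an error in the plan.

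**The case against.** Several points on the other side stand.

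- **Recidivism is undefined and its source unnamed.** Section 13 refers to analysis plans in an original proposal that is not in the supplement. That the outcome rests on the self-interview is the only reading that the documents support, but it is a reading.
- **Not every event is lost.** A reader might infer that observed recidivism will be near zero in both arms whatever the truth. That would require recidivism to mean custody and staff to learn of every detention before the next assessment. Re-arrest without custody is kept, and a short detention first disclosed at an interview is captured by that interview.
- **Intention to treat is not abandoned.** A reader might infer that detained women are removed from the analysis. The Randomization section counts a woman as enrolled once she is assigned, and nothing discards her earlier visits. What is lost is later measurement.
- **Missing data are addressed in general terms.** Section 2.2 and the Data Analyses Plan provide for attrition analyses, nonignorable nonresponse and sensitivity analyses. They could accommodate incarceration, but they do not say that they will.
- **Loss may already be counted.** A reader might add an assumed detention rate to the full 10% and call the trial underpowered. Section 2.3 bases the 10% on 91% retention at 12 months in the earlier WORTH trial. Custody losses may be partly inside that figure; the documents do not say.
- **The rule has a reason.** Section 11.1 keeps prisoners out of the study. That explains no contact in custody. It does not explain why outcomes should not be assessed after release.
- **Adverse event records may not be even between arms.** E-WORTH women attend four more sessions, so staff may hear of more incarcerations in that arm. A remedy that uses these records must deal with this.

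**Conclusion.** The concern holds in a limited form. Followed as written, the plan makes recidivism missing because it occurred when it involves custody that staff know of before the next assessment. The same women lose the 12-month STI test and later behavioural data. No other section repairs this. Complete-case analysis, or imputation that omits the recorded incarceration, would bias a recidivism effect toward zero, and loss on the primary outcomes could differ by arm.

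The size is unknown because no detention rate is given. The 10-point difference shrinking to 1.4 points shows direction under assumed rates and is not an estimate. The power effect is the lesser issue: about 78% at 10% total loss and 74% at 20%, with an unknown part of custody loss already inside the 10%. The outcome-dependent missingness needs no rate to be established. Both copies of the protocol in the supplement carry the same rule, so this is not a difference between versions.

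**What to change.** 1. Reconcile Sections 1.2 and 11.1. Define recidivism and name its data source.
2. Limit discontinuation in Section 11.1 to study contact while in custody. Subject to IRB agreement, allow the remaining outcome assessments after release. Participation in intervention sessions is a separate matter for the sponsor to settle.
3. State that incarcerations recorded as serious adverse events count as recidivism events in the randomised arm.
4. Include recorded incarceration as a predictor in the imputation model for the STI and behavioural outcomes. This can be estimated only if some incarcerated women have later outcomes, which is a further reason for step 2. If the IRB declines post-release assessment, shift the imputed values for these women over a stated range as a sensitivity analysis.
5. Ask about incarceration in the same way in both arms, through the biweekly tracking contacts already planned in Section 3.8. Report recidivism with and without the events that come only from adverse event reports.

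The cost is a protocol amendment with IRB review, one standard question at existing contacts, and a little more analysis. No assessment takes place in custody. Steps 3 to 5 can go ahead even if step 2 is refused.
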